### Follow up procedures

All follow-up assessments will be performed by independent interviewers trained in neurology who are certified according to a standard operating procedure (SOP) and remain fully blinded to treatment allocation throughout the trial. Structured telephone interviews will be conducted standardized CRF forms at 30 and 90 days after symptom onset. The CRFs include mRS and BI scores, stroke recurrence, new-onset vascular events, medication use, and rehabilitation services received during the follow-up period. All interviews will be recorded and saved.

NIHSS assessments will be performed by certified neurologists or neurology residents who have completed standardized NIHSS training. All assessors will be blinded to treatment allocation. Prior to study initiation, assessors will be required to achieve ≥90% agreement with expert consensus scores across 10 validation cases. Throughout the trial, 10% of assessments will be randomly audited by an independent expert, and periodic refresher training will be conducted to maintain inter-rater reliability.

### Data management and quality assurance

The study implements a rigorous data management system with multiple quality control measures. All clinical investigators and research coordinators will receive standardized training on the trial operating procedures before patient recruitment, covering data collection, proper CRF completion, outcome assessment, and serum sample collection. Researchers will verify all CRF entries against source documents for consistency, with modifications clearly documented using lined-through corrections accompanied by signatures and dates.

A critical quality control measure involves the independent double-data-entry system where two separate personnel input the same data to minimize errors. The database then performs automated range and logic checks to identify discrepancies. For quality assurance, regular on-site monitoring visits will be conducted by clinical research associates who will perform source data verification by sampling original records against CRF entries. The monitoring team will also evaluate protocol compliance across all study sites, with findings communicated through monitoring reports and study newsletters to maintain consistent standards.

All research data will be stored securely with multiple backups on different media, while original CRFs will be archived sequentially with a retrieval index. Throughout the study period, investigators will make concerted efforts to maintain patient follow-up. All patient-related information will be stored in locked file cabinets and identified only by coded numbers to protect confidentiality. These comprehensive measures aim to produce high-quality clinical trial data while safeguarding participant rights and data integrity.

A Data Safety Monitoring Board (DSMB), whose members are independent of the trial investigators and free of competing interests, will be established to oversee participant safety throughout the study. The board will review unblinded safety data, including adverse events, laboratory abnormalities, and study discontinuations, and based on its assessments may recommend continuation, modification, or early termination of the trial. All recommendations will be formally documented and communicated to the principal investigator and the institutional review board.

### Sample size calculation

Pilot studies are an essential first step to assess the practicality and feasibility of methods and procedures intended for larger-scale investigation (20–22). They should not be used to estimate effect sizes, to provide power calculations for statistical tests or to perform exploratory analyses of efficacy (20). The present work is a pilot randomized controlled trial (RCT) primarily designed to evaluate the feasibility, safety, and preliminary signal of QHF on the incidence of END in AIS patients. No formal sample size calculation was performed; the target of 36 participants per group was considered adequate for exploring the feasibility of study procedures.

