## Methods

### Study design

The Qingre Huatan Formula for the prevention of early neurological deterioration in acute ischemic stroke (QUIET) trial is a randomized, placebo-controlled, double-blind, parallel-group pilot study registered with ClinicalTrials.gov (NCT06857487) prior to patient enrollment. The primary objective of this study is to assess the effectiveness and safety of QHF vs. placebo for AIS patients at high risk of END. We hypothesize that QHF will be superior to placebo at reducing the risk of END within 7 days of stroke onset, defined as a National Institutes of Health Stroke Scale (NIHSS) score increase of ≥2 points. Furthermore, we will explore the neuroimaging, biological indicators and other dimensions of patients suffering from the phlegm-heat syndrome in AIS. This trial protocol was approved by the institutional review board of Dongzhimen Hospital, Beijing University of Chinese Medicine, Beijing, China (No. 2023DZMEC-410-02). The protocol design is based on the Standard Protocol Items: Recommendations for Interventional Trials (SPIRIT) guidelines (15). The SPIRIT checklist is shown in the Supplementary material.

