No formal interim analysis is planned for this trial. However, an independent Data Safety Monitoring Board will regularly review safety data throughout the study to ensure participant safety. The DSMB may recommend early termination if unexpected safety concerns arise.

All statistics will be evaluated using two-sided tests, and *p* < 0.05 will be considered statistically significant. Statistical analysis will be performed using SAS version 9.4 (SAS Institute Inc.).

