Rooted in thousands of years of continuous development, TCM has accumulated systematic experience in preventing and treating AIS, and it has fostered a number of well-established drugs with verified efficacy. During the past decade, research in this area has accelerated, generating a succession of high-quality clinical evidence that supplies new therapeutic options for this condition (10–12). Our earlier research highlighted the phlegm-heat syndrome as a key pattern in AIS (13). Timely heat-clearing and phlegm-resolving therapy is essential for symptom resolution, neurological recovery, and END prevention (14, 27). Accordingly, we developed the Qingre Huatan Formula (QHF), comprising Gastrodiae Rhizoma, Salviae Miltiorrhizae Radix et Rhizoma, Trichosanthis Fructus, Arisaema cum Bile, Rhei Radix et Rhizoma, Gardeniae Fructus and Acori Tatarinowii Rhizoma. According to traditional Chinese medicine theory, these herbs act synergistically to extinguish wind-phlegm, clear heat and purge the bowels, and open the orifices to unblock collateral circulation.

This study has several strengths in the field of preventing END in AIS. First, we pioneered the use of a RCT design to systematically evaluate the efficacy and safety of traditional Chinese medicine interventions for END. Second, by enrolling only confirmed high-risk END patients, we enhanced the precision of the estimates and statistical power.

We acknowledge that the optimal definition of END remains debated, with no universally accepted threshold, as highlighted in a systematic review (4). While some studies have used a ≥4-point NIHSS increase as the threshold for clinically meaningful deterioration, recent randomized trials published in JAMA Neurology (25, 28) have successfully employed the ≥ 2-point definition as a primary or key secondary endpoint, demonstrating its ability to capture clinically significant treatment effects. Evidence from cohort studies further suggests that a ≥2-point increase is a sensitive predictor of poor outcomes and in-hospital mortality, and this threshold may be particularly appropriate for identifying early deterioration in high-risk populations where timely intervention is critical (29, 30). Future larger trials may consider sensitivity analyses using different END thresholds to further inform this methodological question.

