Nevertheless, certain limitations should not be ignored. First, this is a single-center pilot trial with a relatively small sample size, limiting statistical power. Second, as an exploratory study, it has not yet completed long-term follow-up or multi-center validation, and thus cannot provide high-level evidence for subsequent large-scale trials.

In summary, the QUIET trial aims to determine whether the early initiation of QHF within 48 h of stroke onset reduces the incidence of END in AIS patients compared with placebo. If the results are positive, this study will provide robust evidence for the prevention and treatment of END in AIS, thereby reshaping and optimizing therapeutic strategies for this condition.

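### The sample size section rules out efficacy inference from a pilot and justifies 36 per group by feasibility alone, but the objective, primary test and closing claim are those of an efficacy trial

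*Protocol article*

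**What the plan says.** Under Sample size calculation, the protocol article says of pilot studies: "They should not be used to estimate effect sizes, to provide power calculations for statistical tests or to perform exploratory analyses of efficacy". It describes this trial as "primarily designed to evaluate the feasibility, safety, and preliminary signal of QHF on the incidence of END in AIS patients", reports that no formal calculation was made, and accepts 36 per group as adequate for exploring feasibility.

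Other sections read differently:

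- **Study design** names effectiveness and safety as the primary objective, without mentioning feasibility, and adds: "We hypothesize that QHF will be superior to placebo at reducing the risk of END within 7 days of stroke onset".
- **Efficacy outcomes** makes the END proportion the primary outcome. The secondary, exploratory and safety outcomes that follow are clinical, biological, imaging or adverse-event measures.
- **Statistical analyses** compares END by chi-square or Fisher exact test, reports a risk difference with its 95% interval, tests the secondary outcomes and lists efficacy subgroups. All tests are two-sided, and p<0.05 "will be considered statistically significant".
- **Discussion** credits the enrolment of high-risk patients thus: "we enhanced the precision of the estimates and statistical power". Its limitations paragraph admits limited power and says that the trial cannot supply high-grade evidence. The next paragraph says: "If the results are positive, this study will provide robust evidence for the prevention and treatment of END in AIS", and adds that this would reshape treatment.

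**The concern.** The section that fixes the sample size and the sections that fix the objective, test and conclusion describe two different trials. One is a feasibility pilot that, by its own rule, should not estimate or explore efficacy. The other is a superiority trial with a significance threshold and a strong conclusion attached to a positive result.

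What is at stake is what the trial may conclude. If END does not differ significantly, readers told that superiority was the hypothesis may take this as evidence of no effect. If it does differ significantly, the article has already announced a conclusion that its own sample size rationale does not support. Meanwhile, the question for which 36 per group was chosen has no outcome in the article's lists.

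**Working it through.** **1. The plan's own figure.** The only arithmetic given is 2 × 36 = 72, which is consistent. No power, effect size or planning control rate is stated, so there is no calculation to reproduce.

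**2. Inputs.** n = 36 per arm, 1:1 allocation, two-sided alpha 0.05, chi-square or Fisher test (Randomization, Sample size calculation and Statistical analyses sections). The only END range in the article is 5–40%, given in the Introduction as background and not as a design assumption. The relative reductions below (50%, and 30% as a check) are assumptions of this review.

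**3. Power.** Exact power is the sum, over all 2×2 tables with 36 per arm, of Bin(a; 36, p1) × Bin(b; 36, p2) for tables with p<0.05. The half-width of the 95% interval for the risk difference is 1.96 × √{[p1(1−p1) + p2(1−p2)]/36}. For example, at 30% vs 15% it is 1.96 × √[(0.21 + 0.1275)/36] = 0.190.

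| Control vs QHF | Chi-square power | Fisher power | Half-width (points) | n per arm for 80% power |
|---|---|---|---|---|
| 5% vs 2.5% | 5% | 0.4% | 9 | 906 |
| 10% vs 5% | 13% | 3% | 12 | 435 |
| 20% vs 10% | 22% | 14% | 16 | 199 |
| 30% vs 15% | 33% | 24% | 19 | 121 |
| 40% vs 20% | 47% | 37% | 21 | 82 |

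The last column uses the normal approximation without continuity correction. For a 30% relative reduction, power is at most 20% (chi-square) or 13% (Fisher) over the same range.

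**4. True effect needed for 80% chi-square power.** END would have to fall from 40% to about 12%, from 30% to about 6%, or from 20% to about 1.8%. At a 10% control rate, removing END altogether gives only 49%.

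**5. Observed effect needed for p<0.05.** This is a different quantity from step 4. Take 11/36 control events.

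- With 4/36 on QHF, the difference is 7/36 = 0.194 and the pooled rate 15/72 = 0.208. The standard error is √(2 × 0.208 × 0.792/36) = 0.0957, so z = 2.03 and p = 0.042.
- With 5/36, z = 1.70 and p = 0.089.

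Chi-square significance therefore needs at most 4 events on QHF, an observed relative reduction of at least 1 − 4/11 = 64%. Fisher needs at most 3.

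**6. The precision claim.** Each term p(1−p) rises until p reaches 50%. A higher END rate therefore widens the planned risk-difference interval, as the half-width column shows. Power for a given relative reduction does rise with the control rate.

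**The case against.** The strongest reply is that a pilot needs no sample size calculation, that the article openly includes a preliminary signal among its aims, that safety appears in both statements of purpose, and that an article may leave operational feasibility measures and progression criteria to the full protocol. Much of this stands. The missing calculation is not an error, the mismatch is partial, and the absence of progression thresholds from a condensed article is not a finding. But a preliminary signal does not stretch to a superiority hypothesis judged at p<0.05 and called robust evidence. The objective, hypothesis and outcome lists are stated in the article itself, and they conflict with its sample size section.

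Some stronger readings are tempting but not supported:

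- **That a null result is nearly certain even if QHF works.** For a halving, the chance of a non-significant chi-square result is 67% at a 30% control rate and 53% at 40%. Because entry is restricted to patients at high risk, the low end of the background range is not clearly the relevant one.
- **That significance would need an implausible effect.** The observed effect must be large, but nothing in the article shows it to be implausible.
- **That the Discussion is wrong on both power and precision.** Enrichment does raise power, so only the precision half fails on the planned scale.
- **That feasibility will go unassessed.** The article lists no such outcome; the full protocol, not shown, may.
- **That END at ≥4 points must be added now.** The article defends its ≥2-point threshold and says "Future larger trials may consider sensitivity analyses using different END thresholds". Deferring this is a choice and unrelated to the mismatch.

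The closing claim is Discussion rhetoric rather than an analysis rule, but it tells readers what a positive result will be taken to mean.

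**Conclusion.** The point holds as an internal contradiction that affects what the trial may conclude. The stated rule on pilots and the feasibility-only rationale for 36 per group are incompatible with the superiority hypothesis, the significance threshold and the closing claim. The Discussion also contradicts itself on the grade of evidence. The contradiction rests on the article's wording alone.

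The size of the problem depends on effects assumed here, because the article gives none. For a halving of END, power is under 50% at every control rate examined from 5% to 40%, and at control rates of 10–40% the risk difference would be known only to within about 12 to 21 points. A non-significant result would say little, and a significant one would require a large observed difference.

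**What to change.** 1. **Study design:** state feasibility, safety and a preliminary END signal as the primary objective, and drop the superiority hypothesis.
2. **Sample size calculation:** reword the sentence on what pilots may be used for, so that it permits the END risk difference with its 95% interval as a preliminary, non-confirmatory estimate. Otherwise the planned estimate still breaks the article's own rule.
3. **Statistical analyses:** state that efficacy p-values are descriptive and support no efficacy claim.
4. **Outcomes:** list feasibility measures that planned records already give: recruitment rate per site over the stated enrolment window, Day 90 retention, and completeness of the Day 3, 5 and 7 NIHSS. Sachet adherence has no row in the Table 2 schedule, so on the text shown it would be a new data item.
5. **Discussion:** replace the closing claim with a statement that the results will inform a larger trial, and remove the claim of enhanced precision.

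These changes alter wording and outcome lists and need no extra patients or data. They are most credible if made before results are known. The downside is that the trial can no longer claim efficacy from p<0.05. If the sponsor wants to keep the superiority hypothesis, the trial must be sized for it; for a halving at 80% power that means 82 per arm at a 40% control rate, rising to 906 at 5%.

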### Statistical analyses

Statistical analyses will be conducted using three datasets: the full analysis set (FAS), the per-protocol set (PPS), and the safety set (SS). The FAS will include all randomized participants with at least one post-baseline assessment, with missing data imputed using the multiple-imputation method (23). Sensitivity analyses will be conducted using last observation carried forward (LOCF), worst-case, and best-case scenarios to assess the robustness of the primary outcome under different missing data assumptions. The PPS will comprise only those who fully comply with the protocol without major deviations. The SS will include all participants who receive at least one dose of the study drug and undergo at least one safety evaluation. Both efficacy and safety analyses will follow the intention-to-treat principle. Qualitative variables will be summarized using frequencies and percentages, while quantitative variables will be presented as means ± standard deviations for normally distributed data or medians with interquartile ranges for non-normally distributed data.

For the primary efficacy outcome, the incidence of END will be compared between groups using the chi-square or Fisher exact test, as appropriate. Risk differences and 95% confidence intervals will be reported. Secondary efficacy outcomes such as BI scores, changes in NIHSS scores, and relevant biomarkers will also be compared between groups using Student's *t*-test or the Wilcoxon rank-sum test, with mean differences and 95% confidence intervals reported where applicable. Additionally, the proportion of patients with a mRS grade ≤ 2 and the incidence of AEs will be compared using the chi-square test or Fisher exact test, as appropriate.

Prespecified subgroup analyses for the primary outcome will be performed according to the following baseline characteristics: age (>65 years vs. ≤ 65 years); sex (female vs. male); symptom onset to randomization time ( ≤ 24 h vs. >24 h); medical history (hypertension, diabetes mellitus, coronary heart disease, stroke, and hypercholesterolemia); smoking history; Trial of Org 10172 in acute stroke treatment (TOAST) classification; presence of large artery stenosis; stroke severity based on baseline NIHSS score ( ≤ 5 vs. >5); and severity of phlegm-heat syndrome.

No formal interim analysis is planned for this trial. However, an independent Data Safety Monitoring Board will regularly review safety data throughout the study to ensure participant safety. The DSMB may recommend early termination if unexpected safety concerns arise.

All statistics will be evaluated using two-sided tests, and *p* < 0.05 will be considered statistically significant. Statistical analysis will be performed using SAS version 9.4 (SAS Institute Inc.).

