## Introduction

Stroke is a major global health threat, imposing a substantial burden on individuals and public health systems (1, 2). Ischemic stroke constitutes roughly two-thirds of all new stroke events worldwide (3). Acute ischemic stroke (AIS) is marked by abrupt neurological deficit onset and rapid clinical progression, often culminating in severe disability. Despite guideline-based usual care, however, 5%−40% of patients develop early neurological deterioration (END) within hours or days of symptom onset (4), which is associated with poor clinical outcomes and increased mortality (4–7).

END is one of the most significant challenges in AIS management. Currently, its clinical handling faces three core dilemmas: First, its pathogenesis involves multiple pathophysiological pathways that are intrinsically complex and accompanied by numerous risk factors (8). Second, validated early prediction tools are lacking, impeding rapid identification of high-risk END patients shortly after onset and thereby delaying intensified monitoring and individualized intervention. Moreover, current reperfusion, antithrombotic and neuroprotective strategies show limited efficacy specifically targeting END (9). As a result, the development of safe and effective therapies for this condition has become an urgent unmet need in the acute management of ischemic stroke.

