### Efficacy outcomes

The primary outcome is the proportion of END within 7 days of stroke onset, defined as an NIHSS score increase of ≥2 points compared with baseline. Secondary outcomes are as follows: (1) change in neurological deficit from baseline to 10 days after randomization; (2) the proportion of patients achieving a good functional outcome, defined as a modified Rankin Scale (mRS) score ≤ 2 on day 30 and 90; (3) activities of daily living measured by Barthel Index (BI) on day 30 and 90.

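### The full analysis set requires a post-baseline assessment although intention-to-treat is claimed, so patients lost or dead before one can leave the END analysis for a reason tied to the outcome

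*Protocol article*

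**What the plan says.** All statements below are from the Protocol article.

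- **Analysis set** (Statistical analyses): "The FAS will include all randomized participants with at least one post-baseline assessment", and, for that set, "with missing data imputed using the multiple-imputation method". The kind of assessment that qualifies is not defined. No sentence names the set used for the primary comparison; the full analysis set (FAS) is implied.
- **Principle** (same paragraph): "Both efficacy and safety analyses will follow the intention-to-treat principle".
- **Sensitivity analyses** (same paragraph): "Sensitivity analyses will be conducted using last observation carried forward (LOCF), worst-case, and best-case scenarios". No population is named for them.
- **Primary outcome** (Efficacy outcomes): the share of patients with END in the first 7 days after onset, where END is "defined as an NIHSS score increase of ≥2 points compared with baseline". Death is not mentioned. It appears as an outcome only under Safety outcomes, as a criterion for a serious adverse event and as a grade 5 event.
- **Schedule** (Table 2): NIHSS at baseline (Day 1), Days 3, 5 and 7, and Day 10 or discharge.
- **Safety set** (Statistical analyses): "all participants who receive at least one dose of the study drug", with the further condition of a safety evaluation.

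**The concern.** Requiring one post-baseline value is often harmless. It is less so here, for three reasons.

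- **Timing.** The Introduction says that patients "develop early neurological deterioration (END) within hours or days of symptom onset", and no NIHSS is scheduled between baseline and Day 3.
- **Population.** Only patients at high risk of END are enrolled, and the Introduction links END to increased mortality.
- **Definition.** END exists only as a difference between two NIHSS scores. A patient who cannot be scored has no outcome value, even if the reason is severe deterioration or death.

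Membership of the analysis set can therefore depend on the event that the analysis is meant to count. If such losses differ between arms, the END comparison is no longer protected by randomisation. The trial is a pilot, but Study design states a superiority hypothesis for END and Statistical analyses tests it at two-sided p < 0.05.

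**Working it through.** **1. Text check.** The plan gives no power or sample-size figure to reproduce: Sample size calculation says none was performed, and 2 × 36 = 72 agrees with the stated total. The first question is what happens to each type of patient under the rules as written.

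| Patient | In the FAS? | END value |
|---|---|---|
| Deteriorates, scored on Day 3 or later | Yes | Observed, counts |
| Dies, is transferred or withdraws before any post-baseline assessment | No | None |
| Same, but an adverse-event record or an unscheduled NIHSS exists | Depends on what counts as an assessment | Observed if scored, otherwise imputed |
| Stable on Day 3, dies within 7 days of onset with no recorded rise | Yes | Multiply imputed; non-END under last observation carried forward; END under worst case |

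The second row contradicts intention-to-treat. The third is undetermined. The fourth is not an exclusion, but the primary analysis supplies an NIHSS score for someone who has died.

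**2. Effect on one arm's rate.** Inputs: n = 36 per arm (Sample size calculation). The END count e and the number k of END patients without a post-baseline assessment are assumptions, because the protocol gives neither. The values of e span the 5% to 40% background range in the Introduction, which is a literature range and not a design assumption.

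Shift = (e − k)/(36 − k) − e/36

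| e/36 | k = 1 | k = 2 | k = 3 |
|---|---|---|---|
| 2/36 = 5.6% | 1/35 = 2.9% | 0/34 = 0.0% | not possible |
| 7/36 = 19.4% | 6/35 = 17.1% | 5/34 = 14.7% | 4/33 = 12.1% |
| 11/36 = 30.6% | 10/35 = 28.6% | 9/34 = 26.5% | 8/33 = 24.2% |
| 14/36 = 38.9% | 13/35 = 37.1% | 12/34 = 35.3% | 11/33 = 33.3% |

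The first lost case moves the rate by 1.7 to 2.7 points, and further cases by a similar amount each. Losing a patient who did not deteriorate works the other way: 11/36 = 30.6% becomes 11/35 = 31.4%.

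**3. Effect on the contrast (QHF minus placebo).** The counts are again assumed.

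- No true difference, 11/36 in each arm: losing 1, 2 or 3 END cases from QHF only gives −2.0, −4.1 or −6.3 points.
- A borderline table, 6/36 against 13/36, with the uncorrected chi-square and Fisher exact tests:

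| END cases lost | Difference | Chi-square p | Fisher p |
|---|---|---|---|
| None | −19.4 points | 0.061 | 0.107 |
| 1 QHF | −21.8 points | 0.035 | 0.055 |
| 2 QHF | −24.3 points | 0.018 | 0.025 |
| 1 placebo | −17.6 points | 0.088 | 0.107 |
| 1 in each arm | −20.0 points | 0.051 | 0.093 |
| 2 in each arm | −20.6 points | 0.041 | 0.077 |

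Balanced losses move the difference by about one point or less (0.6 and 1.2). Unbalanced losses move it by 2 to 5 points, in either direction. In a borderline table, one or two patients can carry a p-value across 0.05.

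**The case against.** The strongest reply is that the exclusion may be rare or may not occur. The qualifying assessment is not limited to NIHSS, participants are inpatients, adverse events are recorded from consent onward, and nothing bars an unscheduled NIHSS. An early death might therefore stay in the set. The trial is double-blind with a matched placebo, so there is no particular reason to expect early losses to differ by arm. Rules for death and the imputation model are often left to an analysis plan, and none is shown. The study is a pilot.

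Much of this stands, and it rules out several stronger readings that a reader might infer:

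- *The earliest and worst deteriorations leave the analysis.* They can, but only with no post-baseline assessment at all. Deteriorations scored on Day 3 or later are counted.
- *Excluded patients are also outside the worst-case analysis.* The plan names no population for it. Restriction to the FAS is a plausible reading, not a stated one.
- *The END rate is lowered in both arms.* The direction is not fixed, because early losses unrelated to deterioration raise it.
- *The bias is a known share of the treatment effect.* The protocol assumes no effect size, so no such share can be given.
- *Adverse events will be charged to the wrong arm.* That supposes a dispensing error. Handling one, like ranking deaths in the secondary outcomes, is ordinary analysis-plan detail.

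The reply does not remove the conflict between the FAS definition and the intention-to-treat sentence, since both are in the same paragraph of the current text. Nor does it supply a value for death in an outcome that the article defines by NIHSS alone. The undefined assessment is itself part of the problem, because it decides who is analysed.

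**Conclusion.** The point holds in a limited form. The FAS definition and the intention-to-treat statement contradict each other. With Day 3 as the first scheduled NIHSS and END defined only by NIHSS, the condition allows a patient to leave the primary analysis because of the outcome. A death within the window without a recorded rise is treated as ordinary missing data, which the planned worst-case analysis covers only as a sensitivity check.

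The size is conditional. Each END case lost costs an arm about 2 to 3 points at 36 per arm; the contrast shifts by about 2 to 6 points if one to three losses fall in one arm, and by little if they are balanced. All event and loss counts behind these figures are assumptions, and the documents support no statement on how many such patients there will be or in which direction the comparison would move. The safety wording is a minor companion point: a set restricted to dosed patients cannot follow intention-to-treat as stated.

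**What to change.** 1. Analyse END in all randomised patients, in the arm to which they were randomised.
2. In the primary analysis, count as END any death, or documented neurological worsening that prevents NIHSS scoring, within 7 days of stroke onset. Use the protocol's own window and not the Day 7 visit: Day 1 is baseline, which may fall up to 48 h after onset, so the two do not coincide.
3. Apply multiple imputation only to the NIHSS values that are still missing.
4. State that the best-case and worst-case analyses cover all randomised patients.
5. Limit the intention-to-treat sentence to efficacy.

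**Cost.** No extra patients or visits are needed, but this is more than a change to the analysis-set wording. The endpoint becomes END or death, so its definition must be changed wherever it appears (Abstract, Study design, Efficacy outcomes). The rate changes only slightly if early deaths are few. Worsening that prevents scoring needs a documentation rule that blinded staff can apply. The change should be fixed before unblinding.
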